## Abstract

**Background:**

A large proportion of Syrians have been exposed to potentially traumatic events, multiple losses, and breakdown of supportive social networks and many of them have sought refuge in host countries where they also face post-migration living difficulties such as discrimination or integration problems or both. These adversities may put Syrian refugees at high risk for common mental disorders. In response to this, the World Health Organization (WHO) developed a trans-diagnostic scalable psychological intervention called Problem Management Plus (PM+) to reduce psychological distress among populations exposed to adversities. PM+ has been adapted for Syrian refugees and can be delivered by non-specialist peer lay persons in the community.

**Methods:**

A randomized controlled trial (RCT) will be conducted with 380 Syrian refugees in Turkey. After providing informed consent, participants with high levels of psychological distress (scoring above 15 on the Kessler-10 Psychological Distress Scale (K10)) and functional impairment (scoring above 16 on the WHO Disability Assessment Schedule 2.0, or WHODAS 2.0) will be randomly assigned to Group PM+/enhanced care as usual (Group PM+/E-CAU) (*n* = 190) or E-CAU (*n* = 190). Outcome assessments will take place 1 week after the fifth session (post-assessment), 3 months after the fifth session and 12 months after baseline assessment. The primary outcome is psychological distress as measured by the Hopkins Symptom Checklist (HSCL-25). Secondary outcomes include functional impairment, post-traumatic stress symptoms, self-identified problems, and health system and productivity costs. A process evaluation will be conducted to explore the feasibility, challenges and success of the intervention with 25 participants, including participants, facilitators, policy makers and mental health professionals.

**Discussion:**

The treatment manual of the Syrian-Arabic Group PM+ and training materials will be made available through the WHO once the effectiveness and cost-effectiveness of Group PM+ have been established.

**Trial registration:**

Clinical Trial Registration: ClinicalTrials.gov Identifier NCT03960892. Unique protocol ID: 10/2017. Prospectively registered on 21 May 2019.

## Background

The past eight years have resulted in a great increase of Syrian refugees, and Syria has become the principal contributor to refugees and asylum seekers worldwide [1]. A large proportion of Syrians have sought refuge in neighbouring countries such as Turkey, Jordan and Lebanon, whereas others have fled to Europe [2]. Turkey now hosts 3.6 million Syrian refugees, the largest number of Syrian refugees worldwide [1]. Syrians residing in Turkey are given the status of “under temporary protection” and not “refugee status” by the government of the Republic of Turkey. However, for simplicity, they will be called refugees throughout this article.

Similar to other refugee populations, Syrian refugees may have been exposed to potentially traumatic events such as threats to life, injuries, or witnessing deaths during the war and their flight from conflict [3, 4]. They may face post-migration difficulties such as unemployment, social isolation and discrimination after arriving in a host country [3]. Traumatic events and post-migration difficulties may make Syrian refugees more vulnerable to psychological distress and common mental disorders such as anxiety, depression and post-traumatic stress disorder (PTSD) [5–10]. If left untreated, psychological distress and mental disorders among refugees may become more profound and may create a considerable economic burden for the community [11]. In Turkey, there are currently no evidence-based community-based mental health interventions that Syrian refugees can access and that address their complex mental health needs. Moreover, Turkey lacks Arabic-speaking specialized mental health-care professionals who can deliver such treatments to Syrian refugees. In response to this treatment gap, we adapted a World Health Organization (WHO) psychological intervention called Problem Management Plus (PM+) for Syrian refugees in Turkey.

PM+ is a brief, scalable, trans-diagnostic psychological intervention that has been developed as part of the mental health Gap Action Programme [12]. PM+ addresses symptoms of depression, anxiety, PTSD and psychological distress through cognitive behavioural therapy strategies. Previous randomized controlled trials (RCTs) have demonstrated the effectiveness of individually delivered PM+ in Kenya and Pakistan and of Group PM+ in Pakistan in decreasing depression and anxiety symptoms [13–16]. In Turkey, PM+ is delivered by trained and supervised non-specialist peer refugees who have a minimum of 12 years of education. Using peer-Syrian providers as delivery agents overcomes language issues and has been found to modify the effect on patient outcomes [17]. In Turkey, Group PM+ is being used. Group counselling has been found to be as effective as individual face-to-face sessions [18]. Group sessions also reach more people at one point in time; another advantage is that patients benefit from other group members’ experiences and points of view [19].

The present RCT protocol is part of the larger Syrian Refugees Mental Health Care Systems (STRENGTHS) (https://strengths-project.eu/) [20]. STRENGTHS aims to evaluate the effectiveness and cost-effectiveness of PM+, delivered in group, individual and e-format by conducting eight RCTs in countries neighbouring Syria and in European host countries. STRENGTHS also aims to scale up the delivery and dissemination of PM+ for Syrian refugees in these countries. The PM+ group manual has been translated into Arabic and adapted for Syrian refugees and this work will be presented elsewhere. The adaptation process was carried out in accordance with the Bernal framework, which consisted of the following steps: (a) literal translation by an Arabic-speaking WHO translator, (b) free listening and key informant interviews with Syrian refugees and mental health professionals in order to identify key mental health concepts and problems among Syrian refugees and (c) cognitive testing of the translated manual [21–23].

## Objectives

The main objective of this study is to evaluate the (cost)effectiveness of the culturally adapted version of Group PM+ in adult Syrian refugees with elevated levels of psychological distress in Turkey.

### Design and setting

This study is a two-arm, single-blind RCT comparing Group PM+/E-CAU with E-CAU in 380 study participants (see the flowchart in Fig. 1). It will be conducted in collaboration with the partner non-governmental organization RASASA (Refugee and Asylum Seekers Assistance and Solidarity Association) in the Sultanbeyli District of Istanbul. The Sultanbeyli District is an economically deprived area with more than 23,000 Syrians residing in overcrowded conditions in rented apartment blocks with high levels of poverty and unemployment [24]. RASASA works for the protection of refugees and provides them with psychosocial support and legal assistance. Methods of recruitment include the distribution of various advertisements and documents such as brochures and short movies in addition to social media. The study protocol has been reported in accordance with the Standard Protocol Items: Recommendations for Clinical Interventional Trials (SPIRIT) guidelines (Additional file 1). Figure 1 shows the study flowchart, and Fig. 2 shows the SPIRIT figure.

**Fig. 1 Fig1:**
[figure not shown]
Flowchart of the study

**Fig. 2 Fig2:**
[figure not shown]
Overview of the study measures

### Participant recruitment

#### Participant inclusion criteria

Participants must be adult (18 years or above) Syrians under temporary protection who are Arabic-speaking and residing in Turkey. The inclusion criteria include the following: (1) scoring greater than 16 on the WHO Disability Assessment Schedule 2.0 (WHODAS 2.0) for health and disability and (2) scoring greater than 15 on the Kessler-10 Psychological Distress Scale for psychological distress [25, 26].

#### Participant exclusion criteria

Participants will be excluded if they (1) present with an acute medical condition, (2) have an imminent risk of suicide, (3) have a severe mental disorder (e.g., psychotic disorders or substance dependence) or (4) show severe cognitive impairment (e.g., severe intellectual disability or dementia). Participants excluded from the study will be referred for appropriate treatment and support. Participants found to be eligible will be informed about their eligibility and will be invited to complete a baseline assessment before randomization (−T1).

#### Informed consent

Participants will be invited by the community RASASA for screening. Participants who attend the screening interview will be informed about the study and provided with an informed consent (IC) form which includes the right to withdraw. Participants will be informed about the use of their data and the possibility of sharing relevant data with others for research purposes. Biological specimens will not be collected in this trial. Written or witnessed oral consent (for illiterate participants) will be required before completing screening and baseline assessments.

#### Sample size and power calculations

The Vrije University (VU) University Medical Centre Department of Epidemiology and Biostatistics carried out the power calculations for this study. Considering previous studies with PM+ in Peshawar, Pakistan, and Nairobi, Kenya, we aim for a conservatively estimated small to medium Cohen’s d effect size of 0.4 in the PM+ group at the 3-month follow-up [13, 15]. Power calculations suggest a minimum sample size of 133 participants per group (power = 0.90, a = 0.05, two-sided). Considering an expected 30% attrition at the 3-month follow-up, we aim to include a total number of 380 participants (190 in the Group PM+/E-CAU group and 190 in the E-CAU group).

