#### Randomization

After baseline assessment, participants will be randomly assigned on a 1:1 basis to either Group PM+/E-CAU (*n* = 190) or E-CAU (*n* = 190) (T0). Randomization using computerized software will be carried out by an independent researcher who is not involved in the intervention delivery, clinical supervision, assessments or other aspects of the study.

There is a chance that participants of the study will be recruited from the same household, creating a risk for contamination (if family members were to be allocated to receive different treatments, namely either Group PM+ or E-CAU). To limit the likelihood of contamination, participants from the same household will be assigned to the same intervention arm.

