### Group PM+

PM+ is a brief, trans-diagnostic psychological intervention based on cognitive behavioural therapy techniques and developed by the WHO [12, 27]. It consists of five sessions delivered in five consecutive weeks and aims to reduce symptoms of depression, anxiety, PTSD and related conditions. Groups are separated by gender, and gender-matched facilitators will lead groups consisting of six to eight participants (T1). Sessions include evidence-based strategies of stress management, problem-solving, behavioural activation and strengthening social support. PM+ is designed to be delivered by non-specialist helpers who receive an 8-day training in PM+. These Arabic-speaking non-specialist helpers, who are called facilitators, are supervised by psychologists and psychiatrists who have participated in the PM+ training-of-trainers program. Supervision consists of weekly, face-to-face group supervision and individual supervision when needed.

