## Statistical methods

Descriptive analyses will be carried out in Statistical Package for the Social Sciences (SPSS) and Hierarchical Linear Modelling (HLM) analyses in Stata version 11.2. Across all analyses, two-tailed tests will be reported with a *P* value of less than 0.05. To estimate the effectiveness and cost-effectiveness of Group PM+, the following data analysis methods will be conducted. First, to examine whether there are differences between conditions, *t* tests (continuous variables) or chi-squared test (categorical variables) will be conducted at baseline to compare the two intervention arms (i.e., Group PM+/E-TAU vs. E-TUA) for normally distributed data; Mann–Whitney tests will be conducted for continuous non-normally distributed data.

Intention-to-treat (ITT) analyses, including all randomly assigned participants (*N* = 380) and treatment completers’ (per protocol) analyses, will be conducted. The primary outcomes of the trial will be the ITT analyses. A linear mixed model will be used for the primary endpoint analysis to estimate the intervention effect, which will have intervention as fixed effects, baseline measurement of primary endpoint as covariate, and participants as random effects.

The mean difference between the two treatment arms at each visit/time together with its 95% confidence interval will be derived from the mixed model. A covariate-adjusted mixed model for the primary endpoint will be performed by adding pre-specified covariates at baseline (gender, age, education, traumatic experiences, post-migration difficulties, etc.) into the above model. Missing data will be treated as missing at random. No imputations of missing values will be made, as multilevel models can deal with missing data [40]. Qualitative data from the process evaluation will be analysed thematically in accordance with the framework approach [41]. Interview transcripts will be coded by using Nvivo version 11 [42].

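### The 0.90 power is derived as if all participants were independent, so the derivation does not support that figure for a group-delivered trial that allocates households together

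*Protocol article*

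**What the plan says.** The section on sample size and power targets a "small to medium Cohen’s d effect size of 0.4 in the PM+ group at the 3-month follow-up". It continues: "Power calculations suggest a minimum sample size of 133 participants per group (power = 0.90, a = 0.05, two-sided". The only inflation is for loss to follow-up: "Considering an expected 30% attrition at the 3-month follow-up, we aim to include a total number of 380 participants", that is, 190 per arm.

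Two other sections describe dependence between participants. Under Group PM+, "gender-matched facilitators will lead groups consisting of six to eight participants"; E-CAU participants are not treated in groups. Under Randomization, allocation is 1:1, but "participants from the same household will be assigned to the same intervention arm". That section says only that shared households may occur and gives no number or size.

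The Statistical methods section describes the primary model as having intervention as a fixed effect, with "baseline measurement of primary endpoint as covariate, and participants as random effects". No term for therapy group or household is named.

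**The concern.** People treated in the same group share a facilitator, a schedule and each other, so their outcomes tend to be positively correlated. Members of one household are likely to be correlated as well, and here they always fall in the same arm. Either correlation increases the variance of the treatment difference relative to independent observations. A power figure that ignores both is then too favourable for an analysis that respects the clustering, unless something else compensates.

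The 0.90 is the figure a reader would use to judge what a non-significant result means. If it has no valid derivation, the reader does not know which effects the trial was likely to detect.

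**Working it through.** **Inputs from the document.** d = 0.4; two-sided α = 0.05; power 0.90; 133 analysed per arm; 30% attrition; 1:1 allocation; groups of 6 to 8 in the PM+ arm only.

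**Inputs assumed, because the document gives none.** Group ICC 0.02 to 0.10; baseline–outcome correlation r of 0.3 to 0.5; for illustration only, a mean of 1.3 to 1.5 participants per household with household ICC 0.3.

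**1. Reproducing the plan's figures.** A two-sample t-test with d = 0.4, α = 0.05 and power 0.90 needs 132.3 per group, hence 133. Power at 133 is 0.901. Attrition: 133/0.70 = 190.0 per arm, 380 in total. These steps account for the whole path from d = 0.4 to 380, so no design effect is hidden in it.

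**2. Therapy groups, PM+ arm only.** With about 7 enrolled per group and 30% lost, m = 7 × 0.70 = 4.9 are observed per group. The design effect is DE₁ = 1 + (m − 1) × ICC = 1 + 3.9 × ICC in the PM+ arm and DE₀ = 1 under E-CAU. The noncentrality is 0.4 / √[(DE₁ + DE₀)/133], and power comes from the noncentral t. The effect detectable with 90% power is 0.4 × √[(DE₁ + DE₀)/2].

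| Group ICC | DE₁ | Noncentrality | Power | Detectable d |
|---|---|---|---|---|
| 0 | 1.000 | 3.26 | 0.901 | 0.40 |
| 0.02 | 1.078 | 3.20 | 0.890 | 0.41 |
| 0.05 | 1.195 | 3.11 | 0.873 | 0.42 |
| 0.10 | 1.390 | 2.98 | 0.844 | 0.44 |

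If groups of 7 stayed intact (m = 7), power would be 0.858 at ICC 0.05 and 0.813 at ICC 0.10. At ICC 0.01 with m = 4.9 it is about 0.90, a negligible loss.

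**3. Households, illustration only.** Adding (mean household size − 1) × 0.3 to both DE₁ and DE₀, with mean sizes 1.5 to 1.3, gives power 0.83 to 0.85 at group ICC 0.05 and 0.80 to 0.82 at ICC 0.10. No household input comes from the document.

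**4. Baseline adjustment.** The primary model includes the baseline value of the outcome. Multiplying the variance by (1 − r²), groups only, m = 4.9:

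| Group ICC | r = 0 | r = 0.3 | r = 0.5 |
|---|---|---|---|
| 0.05 | 0.873 | 0.902 | 0.948 |
| 0.10 | 0.844 | 0.876 | 0.930 |

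The r that returns the variance to its independent-observations value solves (1 − r²)(DE₁ + 1)/2 = 1. It is about 0.19, 0.30 and 0.40 at ICC 0.02, 0.05 and 0.10.

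This scaling assumes that the covariate shrinks the between-group component in the same proportion as the rest. If it left that component untouched, the variance sum at ICC 0.10 and r = 0.5 would be 2 × 0.75 + 0.39 = 1.89 instead of 0.75 × 2.39 = 1.79. The noncentrality would be 0.4/√(1.89/133) = 3.36, still above the 3.26 of the independent case.

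**The case against.** The strongest reply is that an unadjusted t-test leaves out two things that work in opposite directions: clustering, which costs power, and the planned baseline covariate, which gains it. A modest correlation restores 90% over the whole range of group ICCs considered. Even with a mean household size of 1.5, household ICC 0.3 and group ICC 0.10, power is 0.80 unadjusted but about 0.90 at r = 0.5. The document gives no r, but it gives no ICC either. This stands. A reader might infer that the trial is underpowered or cannot reach 90% power, and the documents do not support that reading.

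It is also fair that the loss from groups alone is small at low ICCs (about 1 point at 0.02, 3 at 0.05), that the household figures are speculative, and that the calculation contains no arithmetical error. All of this stands too.

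What does not stand is that the matter is merely detail left to a fuller document. The article gives the calculation complete with a definite power, and its numbers match an independent-observations test exactly. Nor can the covariate gain be credited silently: the power paragraph does not invoke it, so its 0.90 was not reached that way.

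**Conclusion.** The point holds as a fault in the derivation. The 0.90 rests on an independence assumption that the article's own sections on Group PM+ and Randomization contradict, and 133 per group leaves essentially no slack to absorb it.

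Without covariate gain, power at d = 0.4 would be about 0.89 to 0.84 over assumed group ICCs of 0.02 to 0.10, with a detectable d of 0.41 to 0.44. It would be lower if shared households are common, which the document does not quantify. With the planned baseline adjustment, power could be at or above 0.90, depending on an r that the document does not state. The therapy-group part is certain by design; the sizes depend on the assumed ICC, retention per group and r.

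The consequence is a planning figure without a valid basis. The point does not show that 380 is too few, and there is no case here for more participants.

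**What to change.** Keep 380 participants and rewrite the power paragraph to state:

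- the expected group size at enrolment and at the primary time point;
- the assumed group ICC, with a range such as 0.02 to 0.10;
- the expected frequency of shared households and the correlation assumed within them;
- the baseline–outcome correlation credited, if any, and its source;
- the resulting power at d = 0.4, or the detectable d at 90% power, over that range.

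The calculation should correspond to a primary analysis that accounts for therapy group (PM+ arm only) and household. The model as described has participants as its only random effect, so its description must be brought into line; otherwise the restated power would belong to an analysis that is not planned.

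The cost is one paragraph and a matching sentence on the model. No participants are added. The stated power may come out slightly less favourable than 0.90, or the same if a baseline correlation is justified.

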#### Randomization

After baseline assessment, participants will be randomly assigned on a 1:1 basis to either Group PM+/E-CAU (*n* = 190) or E-CAU (*n* = 190) (T0). Randomization using computerized software will be carried out by an independent researcher who is not involved in the intervention delivery, clinical supervision, assessments or other aspects of the study.

There is a chance that participants of the study will be recruited from the same household, creating a risk for contamination (if family members were to be allocated to receive different treatments, namely either Group PM+ or E-CAU). To limit the likelihood of contamination, participants from the same household will be assigned to the same intervention arm.

### Group PM+

PM+ is a brief, trans-diagnostic psychological intervention based on cognitive behavioural therapy techniques and developed by the WHO [12, 27]. It consists of five sessions delivered in five consecutive weeks and aims to reduce symptoms of depression, anxiety, PTSD and related conditions. Groups are separated by gender, and gender-matched facilitators will lead groups consisting of six to eight participants (T1). Sessions include evidence-based strategies of stress management, problem-solving, behavioural activation and strengthening social support. PM+ is designed to be delivered by non-specialist helpers who receive an 8-day training in PM+. These Arabic-speaking non-specialist helpers, who are called facilitators, are supervised by psychologists and psychiatrists who have participated in the PM+ training-of-trainers program. Supervision consists of weekly, face-to-face group supervision and individual supervision when needed.

### Enhanced usual care

Syrians in Turkey have free access to mental health services in public hospitals and migrant health centres [28]. However, owing to numerous barriers such as lack of knowledge of available mental health services or (self)stigma, the use of mental health services is low among Syrian refugees [29, 30]. Usual care will be enhanced by providing study participants with a leaflet on publicly available mental health services in the area where they live. Implementing Group PM+ or E-CAU will not require alteration to usual care pathways (including use of any medication) and these will continue for both trial arms.

### Outcome measures

All instruments will be administered by trained research staff blind to the allocation status of the participants at post-assessment (1 week after the fifth PM+ session) (T1), 3 months after the baseline (T2) and 12 months after baseline (T3).

